### Study outcomes

The main study outcome will be the evaluation of the effect of MD during pregnancy on the occurrence of allergic disorders at 24 months of age in the offspring.

Secondary study outcomes will include the evaluation of:

–women MD-adherence score (Med Diet Score);–maternal weight gain and pregnancy complications (including gestational diabetes, arterial hypertension, gestosis, cholestasis, premature rupture of membranes (PROM), placental abruption, post-partum anemia, post-partum hemorrhage);–perinatal complications (including intrauterine growth retardation (IUGR), small-for-gestational-age infant (SGA), large-for-gestational-age infant (LGA), preterm delivery, and fetal malformation) and neonatal birth weight;–body growth indices and occurrence of infectious diseases and chronic non-transmissible conditions (obesity, autoimmune diseases, malignancies, neuropsychiatric disorders) in the first 2 years of age in the offspring;–mother-child pair GM metagenomic and metabolomic features;–exclusive and overall breastfeeding duration and breast milk composition;–epigenetic modulation of genes involved in the regulation of immune system and metabolic pathways in the offspring;–child MD-quality Index score (KIDMED).

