### Statistical methods

All data will be collected in a dedicated database and analyzed by the ST. We will perform intention to treat (ITT) and per-protocol analysis. We will perform ITT analysis by considering the mother-child pair lost after randomization: (1) all missing values of the primary outcome will set to the worst outcome in both groups (equal-case scenario ITT) and (2) missing values of the primary outcome will set to the worst outcome in the Group 1 and to the best outcome in the Group 2 (worst-case scenario ITT). The worst outcome will be defined as the occurrence of ≥1 atopic condition at 24 months, in the offspring; the best outcome will be its opposite. The secondary outcomes will be evaluated using per-protocol analysis. The Kolmogorov-Smirnov test will be used to determine whether variables are normally distributed. Descriptive statistics will be used to summarize baseline characteristics. The Student *t*-test will be used to compare mean values of continuous variables for approximating a normal distribution. For non-normally distributed variables, the Mann-Whitney *U* test will be used. The χ^2^ test or Fisher exact test will be used, when appropriate. We will use a binomial regression model (BRM) to estimate the incidence of the main outcome, i.e., at least one atopic condition at 24 months, in the offspring. The response variable of the BRM will be the presence of at least one atopic condition at 24 months (0 = no; 1 = yes), and the predictor will be the treatment cohort (0 = Group 1; 1 = Group 2). To evaluate the effect of potential confounders on the main outcome, we will add each of them separately to the aforementioned BRM and we will evaluate the changes in the estimated risk ratios. The evaluated potential confounders will be sex (0 = female; 1 = male), age (months), cesarean delivery (0 = no; 1 = yes), born at term (0 = no; 1 = yes), breastfed for at least 2 months (0 = no; 1 = yes), weaning (months), siblings (number), exposed to passive smoking (0 = no; 1 = yes), mother smoked during pregnancy (0 = no; 1 = yes), and exposed to pets (0 = no; 1 = yes), drug use (0 = no; 1 = yes), antiseptics exposure (0 = no; 1 = yes), lifestyle (0 = rural; 1 = urban), dietary habits (0 = low MD-adherence; 1 = medium MD-adherence; 2 = high MD-adherence) and pollution exposure (0 = no; 1 = yes). BRM is among the most commonly suggested methods to report the results from randomized controlled trials with binary outcomes. Regression modeling allows adding baseline co-variables to increase the precision of the estimate and better control for potential confounders. Comparisons of taxa or gene abundance between groups will be carried out using pairwise Wilcoxon tests. Statistical significance of pangene prevalence will be verified through Fisher’s test with multiple-hypothesis testing corrections *via* the false discovery rate (FDR). Machine learning-based classification analysis will be done using the MetAML package (30) and by considering random forests (RFs) as back-end classifier for all the results. Results will be obtained through a fivefold cross-validation and averaged on 20 independent runs. To evaluate whether the significant associations for the cord blood analysis primarily reflect maternal adherence to MD, additional models adjusted for cord blood DNA methylation of the same CpG site and for miRNAs will be evaluated when examining the association between DNA methylation/miRNAs and childhood allergic sensitization. For DNA methylation, using a reference methylation Quantitative Trait Loci (QTL) library, we will evaluate the genetic control of methylation for the top 30 associated CpG sites identified from the mid-childhood meta-analysis for atopic sensitization, environmental and food allergen sensitization. We leveraged genetic-epigenetic information from the ARIES large-scale genome-mQTL analysis, which included 1,000 mother-child pairs^2^ (31). mQTL comparisons will be focused on the *cis* position (i.e., a genetic variant within ±500 Kb of a methylation locus) measured from cord blood, and with MAF ≥5%. The level of significance for all statistical tests will be two-sided, *p* < 0.05. An integrative approach that combines multi-omics data together with integrated clinical data analysis will be performed. Multivariable linear regression will be used to analyze associations differentially methylated regions in cord blood DNA with clinical measures of offspring. All significance values will be corrected to take into account the effect of multiple comparisons, using the Bonferroni adjustment. All analyses will be performed with Stata 16.1 (Stata Corporation, College Station, TX, USA), SAS^®^ version 9.4 (SAS Institute, Inc., Cary, NC, USA) and R version 3.4.1.

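### Caesarean delivery, term birth, breastfeeding and weaning arise after randomisation but are listed as confounders in the one-at-a-time adjusted models of the primary outcome, and MD-adherence is listed with no time point

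*Protocol article*

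**What the plan says.** All of this is in the Protocol article. The Statistical methods section models the occurrence of at least one atopic condition at 24 months by binomial regression, "and the predictor will be the treatment cohort (0 = Group 1; 1 = Group 2"). No covariate is in that model.

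A second step concerns potential confounders: "we will add each of them separately to the aforementioned BRM and we will evaluate the changes in the estimated risk ratios". Fifteen are listed. Among them are "cesarean delivery (0 = no; 1 = yes), born at term (0 = no; 1 = yes), breastfed for at least 2 months", then weaning in months and, near the end, "dietary habits (0 = low MD-adherence; 1 = medium MD-adherence; 2 = high MD-adherence"). The reason given is that "Regression modeling allows adding baseline co-variables to increase the precision of the estimate and better control for potential confounders".

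Three other sections bear on this:

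- Study outcomes lists as secondary outcomes "women MD-adherence score (Med Diet Score"), "exclusive and overall breastfeeding duration and breast milk composition", and preterm delivery among the perinatal complications.
- Background and rationale gives the hypothesis that counselling limits allergy in the child by improving the mother's adherence to the diet.
- Data and sample collection has the Med Diet Score taken at enrolment and again at later pregnancy visits, in the low, medium and high categories that the covariate uses.

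**The concern.** Randomisation makes the groups comparable in expectation on everything fixed beforehand. A variable that arises afterwards cannot confound the comparison. If counselling affects it, it lies on the path from counselling to allergy, and conditioning on it takes away part of the effect being estimated. If it also shares unmeasured causes with allergy, conditioning can introduce bias.

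The only meaning the plan gives to a change in the risk ratio is that the added variable is a confounder. If the trial works as hypothesised, adding on-study adherence would shrink the effect, and a reader following the plan would conclude that the crude result was confounded by diet. The same applies to breastfeeding or term birth if counselling changes them, and the protocol allows for that by naming both as outcomes. The fifteen adjusted risk ratios also come with no rule for interpreting a change.

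**Working it through.** **1. The plan's own figure.** The inputs are 30% versus 15%, two-sided alpha 0.05, power 0.80 and drop-out up to 15% (Sample size calculation).

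- Pooled variance: [1.96·√(2·0.225·0.775) + 0.842·√(0.30·0.70 + 0.15·0.85)]² / 0.15² = 120.5 per group, and 120.5 × 1.15 = 138.5.
- Unpooled variance: (1.96 + 0.842)² · 0.3375 / 0.15² = 117.7, and 117.7 / 0.85 = 138.5.

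Either route reproduces 138 per group. This is an unadjusted comparison, so the sample size does not depend on the covariate list.

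**2. Timing of the listed variables.** Women are enrolled and the first counselling session is held at 8–13 gestational weeks (Eligibility criteria; Interventions).

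| Covariate | When it can arise | Also a secondary outcome? |
|---|---|---|
| Caesarean delivery | At delivery | No |
| Term birth | At delivery | Yes, as preterm delivery |
| Breastfed at least 2 months | After delivery | Yes, as breastfeeding duration |
| Weaning age | After delivery | No |
| Dietary habits (MD-adherence) | Not stated; scored at enrolment and later | Yes, as Med Diet Score |

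The first four are after randomisation without exception, so the stated reason, baseline covariates, does not fit them. The fifth fits that reason only if it is the enrolment score.

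**3. What adjusting for on-study adherence would do.** The total effect, Group 1 versus Group 2, is RR = 0.15/0.30 = 0.50. Assume a log-linear model, and let a share s of the log risk ratio run through adherence measured after counselling begins. The treatment coefficient left after adding adherence is (1 − s)·ln 0.50, so the adjusted RR = 0.50^(1 − s).

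| Assumed share s | Adjusted RR, Group 1 vs 2 | In the plan's coding (1 = Group 2) |
|---|---|---|
| 0% | 0.50 | 2.00 |
| 25% | 0.59 | 1.68 |
| 50% | 0.71 | 1.41 |
| 75% | 0.84 | 1.19 |
| 100% | 1.00 | 1.00 |

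A check at s = 50%, with assumed adherence (low/medium/high) of 10/30/60% in Group 1 and 50/40/10% in Group 2:

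- Category risks are 0.260/0.176/0.119 in Group 1 and 0.368/0.249/0.168 in Group 2.
- Group 1 overall: 0.10·0.260 + 0.30·0.176 + 0.60·0.119 = 0.150.
- Group 2 overall: 0.50·0.368 + 0.40·0.249 + 0.10·0.168 = 0.300.
- The crude RR is 0.50, while within each category it is about 0.71 (for example 0.260/0.368).

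The crude estimate is right for every s; only the adjusted one moves.

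**4. Bias when counselling has no effect on allergy.** Assume that counselling raises the log odds of breastfeeding by 1.0, and that an unmeasured factor present in half the mothers raises it by 1.0 or 1.5 and multiplies allergy risk by e^−0.5 = 0.61 or e^−0.75 = 0.47. In a large simulation (2,000,000 pairs), adjusting for breastfeeding moved the RR from 1.00 to 1.02 or 1.05. A separate simulation gave about 1.08. For scale, with 138 per group and 30% risk in both, SE(ln RR) = √(2·0.70/(0.30·138)) = 0.18. Since ln 1.08 = 0.077, the largest of these shifts is about 0.4 of a standard error.

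**The case against.** The strongest reply is that the primary analysis is not touched, and that is correct. The main model contains treatment alone, the sample size rests on an unadjusted test, and the covariates enter singly as a secondary check. No threshold, variable selection or replacement of the main estimate is stated. A reader might infer from the confounder list that the primary model is itself adjusted for post-randomisation variables; the text does not say so.

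Three further inferences go beyond the document:

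- **That MD-adherence is certainly a post-randomisation covariate.** Its time point is not given, and the enrolment score would be legitimate. What stands is that the timing is left open for the very variable the intervention targets.
- **That adjustment would abolish the effect.** An adjusted RR of 1.00 requires all of the effect to run through the covariate. Nothing in the document fixes that share, hence the range.
- **That an ineffective intervention would look effective.** The shifts in step 4 are under half a standard error and, under those assumptions, go against counselling. They also need counselling to change breastfeeding, although the Interventions section has it encouraged in both groups.

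None of this rescues caesarean delivery, term birth, breastfeeding or weaning as confounders.

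**Conclusion.** The point holds for the secondary, one-at-a-time adjusted models. Four listed variables are post-randomisation by nature, two of those match the protocol's own secondary outcomes, and the plan's stated rationale does not describe them. A fifth, MD-adherence, is acceptable or not depending on a time point that the plan omits.

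The treatment-only risk ratio and the sample size are unaffected. The adjusted risk ratios would not estimate the total effect of counselling: a true 0.50 could appear as anything from 0.59 to 1.00 if 25 to 100% of the log effect ran through on-study adherence. Those shares, and the log-linear form, are assumptions. The size of any distortion from the birth and feeding variables cannot be derived from the document. The correction is worth making because the plan invites this attenuation to be misread as confounding, but it does not put the primary conclusion at risk as long as the treatment-only estimate remains primary.

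**What to change.** In the Statistical methods section:

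1. State that the treatment-only risk ratio, or one pre-specified baseline-adjusted risk ratio, is the primary estimate.
2. Restrict adjustment to variables fixed at randomisation, for example the BMI and parity strata, the enrolment Med Diet Score, and exposures such as smoking and pets as recorded at enrolment. Infant sex may be added, since counselling cannot alter it.
3. State that dietary habits means the enrolment Med Diet Score.
4. Remove caesarean delivery, term birth, breastfeeding and weaning from the confounder list, and exclude follow-up MD-adherence from it. Report these only in a separately labelled exploratory mediation analysis that does not bear on the primary conclusion.

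Item 4 needs its own text. The mediation analysis announced under Epigenetic analyses links MD-adherence, epigenetic markers and clinical outcome, and does not cover the birth or feeding variables.

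The cost is wording in the protocol or analysis plan. No new data are needed: BMI and parity are known at randomisation, and the Med Diet Score, smoking exposure and pets are already collected at baseline. The change should be made before the Statistical Team analyses the outcome data.

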### Data and sample collection

At baseline, after the first evaluation by the RT and the collection of written informed consent form, the CT will collect the following variables in a dedicated chart: anamnestic and clinical features, personal and anthropometric data, socio-demographic factors, gestational age, allergies, number of cohabitants, pets, sports activities, use of drugs, smoking exposure, education level, family and living conditions. At enrollment a validated questionnaire on MD-adherence (Med Diet Score) and a 7-day food diary (five weekdays and two weekend days) will be collected. The 7-day food dairy data will be analyzed using specific software (Winfood–Medimatica Srl) by a dietitian. The intake of drugs, dietary supplements, pre-, pro-, and synbiotics will be recorded in the same chart. Then, the RT will schedule for each participant follow-up visits every 12 weeks from the enrollment (8–13 GW), then at 14–28 GW and at 29–40 GW. During these visits the CT will perform a full physical examination, anamnestic and clinical data collection, stool sampling (at least 3 g), 7-day food diary collection, Med Diet Score assessment. Each item assigns a score of 0 or 1, with a total score ranging from 0 to 14. The three categories of adherence to MD are divided in ≤5 (low), 6–9 (medium), ≥10 (high) score. Furthermore, to ensure and encourage the completion of the 7-day food diary, one week before each visit, the RT will remind the women by a phone call to fill in the food diary daily for the following week and to return them at the following visit. At delivery a cord blood sample (at least 10 ml) and a breast milk sample (collected within 24 h after delivery) (3 ml) will be collected. All neonatal clinical features will be evaluated by CT. After delivery, for all babies a follow-up visit will be planned every 3 months for the first 12 months of life and then every 6 months until the age of 2 years. At each visit the following procedures will be adopted by CT: full anamnestic and clinical evaluation, body growth assessment, occurrence of allergic disorders, occurrence of other conditions, 7-day food diary, child Mediterranean Diet Quality Index score (KIDMED) evaluation, stool sampling (at least 3 g). At each visit the persistence of breastfeeding will be also assessed and a breast milk sample will be eventually collected (3 ml). In addition, Skin Prick Testing using main pediatric allergens will be performed at 12 and 24 months. All collected data and documents will always remain confidential.

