Global methylome analysis will be performed using Epigenome-Wide Association Study (EWAS) approach. Infinium TM Methylation EPIC Bead Chip by Illumina (San Diego, CA, USA) will be used to explore over 8,50,000 methylation sites per sample at single-nucleotide resolution, according to the manufacturer’s protocol.

For miRNA expression analysis, RNA will be extracted from the second EDTA tubes using Trizol protocol (Invitrogen, Life Technologies Europe BV, Monza, Italy) and TaqMan^®^ Array Human MicroRNA A Card v2.0, contains 384 TaqMan^®^ MicroRNA Assays, enabling accurate quantization of 377 human microRNAs (Applied Biosystem) will be used.

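### The methylation-QTL lookup takes its CpG sites from a mid-childhood meta-analysis that the trial does not contain, so no genetic-control check is planned for PREMEDI's own cord-blood sites

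*Protocol article*

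**What the plan says.** In the Protocol article, Statistical methods, the step is described as follows: "using a reference methylation Quantitative Trait Loci (QTL) library, we will evaluate the genetic control of methylation". The sites to be looked up are the "top 30 associated CpG sites identified from the mid-childhood meta-analysis for atopic sensitization, environmental and food allergen sensitization". The library is external: "We leveraged genetic-epigenetic information from the ARIES large-scale genome-mQTL analysis, which included 1,000 mother-child pairs". Comparisons are restricted to cis variants (within 500 Kb either side of the methylation locus), to cord-blood measurements, and to a minor allele frequency of at least 5%.

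The trial's own epigenome-wide work is under Epigenetic analyses: "Global methylome analysis will be performed using Epigenome-Wide Association Study (EWAS) approach". It uses an array of over 850,000 sites on DNA from cord blood taken at delivery.

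Under Data and sample collection, child visits run "every 3 months for the first 12 months of life and then every 6 months until the age of 2 years", and "Skin Prick Testing using main pediatric allergens will be performed at 12 and 24 months".

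**The concern.** The rule refers to a particular analysis as if the reader already knew it. Its age range lies beyond the end of follow-up, and its type (a meta-analysis) does not fit a single trial. An analyst holding PREMEDI data cannot produce the list of 30 sites from the rule as written.

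At stake is how methylation associations are read. A lookup of this kind flags sites where a known genetic variant influences methylation. If a flagged site is also associated with allergy, inherited genotype may explain both. Every child in the trial has a first-degree relative with documented allergic disease (Eligibility criteria), so inherited predisposition is a live explanation. If the lookup is tied to a list from elsewhere, the sites that PREMEDI itself reports are not flagged.

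**Working it through.** No sample size, power or error rate is involved, and the count of 30 is a choice with no inputs to reproduce it from. The check is a comparison of what the rule needs with what the article provides.

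1. **A mid-childhood time point.** Follow-up ends at 2 years. The main outcome is at 24 months (Study outcomes), and the last skin prick test is at 24 months. There is none.

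2. **A meta-analysis.** Study design describes one multi-centre, parallel-group randomised trial. No pooling of cohorts is described anywhere in the article.

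3. **A named outside source.** No citation is attached to the phrase. The reference that follows (31) belongs to the next sentence and to the QTL library. The library supplies links between variants and methylation; the article does not present it as the source of the 30 sites.

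4. **Methylation at a later age.** Epigenetic analyses describes methylation in cord blood only, for both the targeted sequencing and the array. No later blood sample for methylation appears under Data and sample collection.

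5. **A lookup elsewhere for the trial's own sites.** Statistical methods plans multivariable linear regression of differentially methylated cord-blood regions on clinical measures of the child. Epigenetic analyses plans to link diet adherence, biomarkers and clinical outcome, partly by mediation analysis. Neither has a QTL step attached. The one in question is the only one in the article.

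6. **The neighbouring sentence.** Just before the QTL step, models relating methylation to childhood sensitisation are to be adjusted for cord-blood methylation at the same CpG site. With cord blood as the only tissue, the exposure M and the adjustment variable are the same measurement. The model S = b0 + b1·M + b2·M identifies only the sum b1 + b2, so the adjusted effect is not estimable. The adjustment makes sense only if M is also measured later, which this trial does not plan. Two consecutive steps thus presuppose data that the described design does not collect.

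7. **Which analyses are exposed.** Allocation is randomised 1:1 (Allocation and blinding), so the child's genotype is balanced between groups in expectation. A methylation difference between randomised groups is therefore not confounded by genotype, apart from chance imbalance, selective loss, or the per-protocol restriction applied to secondary outcomes. Associations of methylation with sensitisation, allergic outcome or observed adherence are not randomised, and neither is the link from mediator to outcome in the mediation analysis. Those are where the missing lookup counts.

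**The case against.** The best defence is that the step is a lookup, not a re-analysis. It needs a list of sites and a library, and a list from outside work on allergic sensitisation is a legitimate set of candidate sites. An article may leave the source of such a list to the full protocol. The feasibility part stands: a reader might infer that the step cannot be run at all, and that is not so if an external list is supplied. But the article does more than omit a source. It states a specific selection rule that conflicts with the design it describes. An external list, even once named, would still leave the trial's own sites without a planned lookup, except where one of them happened to be on that list.

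A reader might also infer that a genetic signal could be passed off as an effect of the diet intervention. The article does not support that for the randomised comparison, for the reason in step 7 of the working. Nor does it say that the lookup is meant to separate genotype from diet. The question about maternal adherence sits in the preceding sentence, while the lookup is tied to sensitisation.

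A reader might further infer that both sentences were carried over from another study. The article does not show where they came from, and the point does not depend on it.

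Finally, the step is peripheral. Epigenetics is one of eight secondary outcome items, and the epigenome-wide part is presented as exploratory. That stands and sets the severity.

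**Conclusion.** The point holds, at minor severity. As written, the rule cannot draw its sites from PREMEDI's results, and no genetic-control lookup is planned for the trial's own cord-blood sites. The effect is confined to interpretation of the non-randomised methylation associations and the mediation analysis. The randomised between-group comparison is largely protected, and the primary outcome, its model and the sample size are untouched. No numerical bias can be derived from the article, and none is claimed.

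The conclusion assumes that methylation is measured only in cord blood and that children are not followed beyond 24 months, as the article describes. If the full protocol names an external list, the question of its source is settled, but the missing lookup for the trial's own sites remains unless that document adds it.

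**What to change.** Replace the source of the sites with: *the top 30 CpG sites from the PREMEDI cord-blood EPIC analysis associated with skin-prick sensitisation (atopic, environmental and food allergens) at 24 months*. Keep the same library, cis window and allele-frequency limit. State whether the 30 are one ranking or one per type of sensitisation. Any lookup for sites associated with diet adherence or with the primary outcome should be a separate list, so that different rankings are not pooled under one count.

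If an external list is intended, name it, say why its sites are used, and add the lookup for the trial's own sites.

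Correct the neighbouring sentence in the same amendment: either remove the adjustment for cord-blood methylation where cord-blood methylation is itself the exposure, or say which later measurement is meant.

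The cost is one or two sentences. The replacement uses data and a library already in the plan, with no new samples.

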### Sample size calculation

Based on the results of the EUROPREVALL cohort (29), reporting a cumulative incidence for allergic diseases of 30%, and on the results of a previous pilot study performed at our center (unpublished data) showing a drop-out rate to this kind of intervention up to 15%, we estimated that 138 mother-child pair per group will be needed to detect a reduction in cumulative incidence of at least one allergic disease at 24 months from 30 to 15%, with a power of 0.80 at an alpha level of 0.05 (Pearson’s Chi-square, two-tailed test).

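### The sentence that Bonferroni-corrects all significance values contradicts the FDR rule and, read literally, reaches a primary test sized at unadjusted 0.05; the same-CpG adjustment enters one variable twice

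*Protocol article*

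**What the plan says.** **Significance rules.** The protocol article's Statistical methods section gives three statements:

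- Pangene prevalence is tested by Fisher's test "with multiple-hypothesis testing corrections", using the false discovery rate.
- "The level of significance for all statistical tests will be two-sided", at p < 0.05.
- "All significance values will be corrected to take into account the effect of multiple comparisons, using the Bonferroni adjustment". This directly follows the sentence on regressing clinical measures on methylated regions in cord blood. It names no family and no number of comparisons.

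The Study outcomes section names one main outcome. The Sample size calculation plans it for 30% versus 15%, "with a power of 0.80 at an alpha level of 0.05", by a two-tailed Pearson chi-square test with drop-out up to 15%. The result is 138 pairs per group.

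**Methylation model.** To judge whether cord blood associations mainly reflect maternal adherence to the Mediterranean diet (MD), Statistical methods says that "additional models adjusted for cord blood DNA methylation of the same CpG site and for miRNAs will be evaluated" when methylation or miRNAs are related to childhood allergic sensitisation. It then looks up genetic control for "the top 30 associated CpG sites identified from the mid-childhood meta-analysis for atopic sensitization". The methylation material is described under Data and sample collection ("At delivery a cord blood sample (at least 10 ml") and under Epigenetic analyses. Child follow-up runs to the age of 2 years.

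**The concern.** A pangene test cannot be governed by FDR if every significance value in the trial is Bonferroni-corrected, so one of the two statements must give way.

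The word *All* matters more for the primary outcome. If it is taken at face value, the primary p-value is multiplied by an unstated m, although the trial was sized without any such correction. A primary p-value between 0.05/m and 0.05 would then count as positive on one reading and negative on the other, and the choice could be made after the result is known.

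The same-CpG adjustment is a separate problem in the exploratory omics work. It is offered as the check on maternal diet, but with the material described it checks nothing.

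**Working it through.** **1. Reproduce the planned sample size.** Inputs from the Sample size calculation: p1 = 0.30, p2 = 0.15, two-sided alpha 0.05, power 0.80, drop-out 15%.

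Unpooled two-proportion formula: n = (z_alpha + z_power)² × [p1(1−p1) + p2(1−p2)] / (p1−p2)²

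- Variance sum: 0.30×0.70 + 0.15×0.85 = 0.3375
- Divided by 0.15² = 0.0225, this gives 15
- (1.960 + 0.842)² = 7.849, so n = 7.849 × 15 = 117.7
- 117.7 / 0.85 = 138.5, against the stated 138

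The same formula at alpha 0.025 (Bonferroni with m = 2) gives (2.241 + 0.842)² × 15 = 142.6, or 167.7 after drop-out. The stated 138 therefore fits an uncorrected primary test and does not fit even the mildest correction.

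**2. Primary power if the Bonferroni sentence is applied literally.** Evaluable pairs: 138 × 0.85 = 117 per group. With pooled variance under the null:

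power = Φ{ [ |p1−p2|√n − z √(2p̄(1−p̄)) ] / √[p1(1−p1)+p2(1−p2)] }

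Here p̄ = 0.225, √(2×0.225×0.775) = 0.5906, √0.3375 = 0.5809 and 0.15×√117 = 1.6225.

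| Assumed m | alpha | z | (1.6225 − z×0.5906)/0.5809 | Power at 117 | Power at 138 |
|---|---|---|---|---|---|
| 1 | 0.05 | 1.960 | 0.80 | 0.79 | 0.85 |
| 2 | 0.025 | 2.241 | 0.51 | 0.70 | 0.78 |
| 5 | 0.01 | 2.576 | 0.17 | 0.57 | 0.66 |
| 9 | 0.0056 | 2.773 | −0.03 | 0.49 | 0.59 |

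The value m = 9 counts the one primary outcome and the eight secondary items in Study outcomes as one test each. Several of those items bundle more than one outcome, so this is an illustration and not the plan's own figure.

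For 80% power by the pooled formula with 15% drop-out, the numbers per group would be 143 (m = 1), 173 (m = 2), 212 (m = 5) and 237 (m = 9).

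**3. The same-CpG model.** Epigenetic analyses takes DNA and RNA from two cord blood tubes. The child visits under Data and sample collection list stool, breast milk and skin prick testing. Serum specific IgE appears among the food allergy tests, but no methylation assay on a later sample is described. Each child therefore has one methylation value M per site. With S for sensitisation, the planned model is

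logit P(S = 1) = b0 + b1·M + b2·M = b0 + (b1 + b2)·M

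The design matrix has three columns and rank two. Only the sum b1 + b2 can be estimated. Software that drops the redundant column would return the unadjusted model labelled as adjusted. No diet variable appears in it, although randomised group and the maternal Med Diet Score are both available.

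**4. The mid-childhood source.** Follow-up ends at 24 months, so a mid-childhood meta-analysis cannot come from this trial. The article does not say which one is meant.

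**The case against.** **On the significance rules.** A reader might infer that the primary alpha is undefined. The documents do not support that: the Sample size calculation gives two-sided 0.05, Statistical methods repeats p < 0.05, and 138 per group fits that level. Nor are the p < 0.05 rule and Bonferroni incompatible in themselves, since Bonferroni-adjusted p-values can be compared with 0.05. The position of the Bonferroni sentence suggests that it was written for the omics analyses. It is also fair to say that lists of multiplicity families are usually left to the analysis plan, and their absence is not held against the article. All of this stands. It does not remove the stated scope, which is all values, or the clash with FDR.

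**On false positives.** A reader might infer that over 850,000 sites will be tested uncorrected, giving about 0.05 × 850,000 = 42,500 false findings. The placement of the sentence argues against that reading, because the methylation analyses are what it most plainly covers.

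**On the CpG model.** The article is condensed, and the sentence might presuppose a later methylation measurement, which would make the adjustment estimable. No such measurement is described, and even then the model would contain no diet term. The adjustment for miRNAs in the same sentence is estimable and is not criticised here. Epigenetic analyses also plans a mediation analysis linking MD adherence, biomarkers and outcome. It would therefore be wrong to infer that the trial cannot examine maternal diet at all. That analysis does not repair this model.

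**On the choice of methods.** Bonferroni is valid for the omics work, and choosing CpG sites from an external source is legitimate. Requiring another procedure, or selection within the trial, would be a preference.

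**Conclusion.** The point holds in limited form.

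- The Bonferroni sentence contradicts the FDR rule for pangene prevalence.
- Its literal scope includes a primary test that was sized without correction. The primary alpha is stated as 0.05; what is unclear is whether the primary is exempt from the sentence. If it is exempt, nothing changes. If it is not, power at 117 per group falls from 0.79 to 0.70 for m = 2 and to 0.49 for m = 9. These figures rest on the planned 30% and 15%, on 15% loss, and on assumed values of m. They leave out the planned imputation of missing primary outcomes.
- The same-CpG adjustment cannot be estimated from the material described and does not address maternal diet. This rests on cord blood being the only methylation sample, which is all that the article describes.
- The mid-childhood meta-analysis is external and unidentified. Using an external source is not an error, but the reference cannot be followed as it stands.

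The first two items bear on how the primary result is read. The last two concern exploratory work only.

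**What to change.** Before the database is locked and groups are revealed:

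1. State that the single primary comparison is tested at two-sided 0.05 without multiplicity correction. Say in one clause how the clinical secondary outcomes are read, for example as supportive with confidence intervals.
2. Limit the Bonferroni sentence to the cord blood methylation and miRNA analyses, and keep FDR for the metagenomic tests. Name the taxon and gene abundance comparisons there too, since no method is now attached to them specifically.
3. Delete the same-CpG adjustment. Fit sensitisation on cord blood methylation with and without randomised group and maternal Med Diet Score, and compare the methylation coefficients. If a later methylation sample does exist, describe it.
4. Identify the mid-childhood meta-analysis or remove the reference.

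The cost is a wording change in the protocol or analysis plan. Sample size, visits and sampling stay as they are.
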